#### ***Surface electromyographic data***

Five seconds of the signal will be used for the calculation of the root mean square (RMS) of the amplitude, with the two initial seconds and final one second of the eight-second reading discarded. For data recorded in the resting position and during maximal intercuspation, the RMS will be calculated using a 200 ms moving window.

The data recorded during chewing will be normalized by the peak EMG recorded from the same isotonic trial (dynamic mean method). The amplitude of the signal obtained in the resting position and during maximal intercuspation will be expressed as percentage of the average RMS recorded in the three readings during maximum voluntary contraction (MVC) (%MVC).

All stabilometric and EMG signals will be processed performing specific routines carried out in the Matlab program, version 7.1 (The MathWorks Inc., Natick, MA, USA).

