Studies have suggested that massaging the muscles of mastication, joint mobilization, manual therapy, mandibular exercises, biofeedback and the application of electrophysical resources may be effective in the treatment of TMD [22-26]. Joint mobilization has proven effective at reducing pain, disability and local ischemia [27], breaking fibrous adhesions, enhancing the extensibility of non-contractile structures, increasing the range of motion, enhancing the transmission of afferent information through the stimulation of mechanoreceptors and stimulating proprioception and the production of synovial fluid [27,28]. The use of joint mobilization has been tested on individuals with TMD, in whom a reduction in pain and increased mandibular range of movement (ROM) have been reported [29-32].

Massage has proven effective at diminishing EMG activity and pain [19,21], preventing the formation of connective tissue adherences, enhancing the production and circulation of endogenous opioids [19], increasing local blood flow, facilitating the elimination of residual substances and extracellular fluid, improving the nutrition of myofibrils and promoting relaxation and a sensation of wellbeing [33,34]. Massaging the muscles of mastication has been administered to patients with TMD, leading to a reduction in pain, an increase in mandibular ROM and a decrease in EMG activity in the muscles [21,35].

Postural control may be related to afferent signals of the trigeminal nerve, which depend on information from receptors of the stomatognathic complex (dentoalveolar ligaments, muscle and joint receptors). Moreover, TMD may alter muscle activity and the positioning of structures of the stomatognathic system, interfering in the information transmitted for the control of posture. Thus, relaxation of the muscles of mastication (as assessed through surface EMG) and the alignment of joint structures (assessed through a clinical exam) may alter afference from the receptors of the stomatognathic system, thereby affecting postural control (assessed through stabilometry). Based on this hypothesis, the aim of the proposed study is to determine the effect of facial massage and mandibular mobilization on EMG activity of the muscles of mastication and static balance in individuals with TMD.

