#### ***Surface EMG***

Surface EMG signals from the right and left masseter and right and left anterior temporal bundle will be recorded with disposable surface electrodes (Ag/AgCl - Noraxon^®^ - http://noraxon.com - [name]. [contact]) attached to the belly of the muscle in the region with the greatest tonus after the volunteer performs moderate intercuspation (clenching of the teeth). The inter-electrode distance will be 20 mm from center to center. The sites for the electrodes will be cleaned with a cotton ball soaked in alcohol to diminish the impedance between the skin and electrodes [39]. A rectangular metallic electrode measuring 3 cm × 2 cm coated with Lectron II conductive gel (Pharmaceutical Innovations^®^ - http://www.pharminnovations.com - [name] [name]) to increase the conduction capacity and impede interference from external noise will be attached to the left wrist of the volunteers for reference.

The bipolar EMG signals will be amplified using an eight-channel module (EMG System do Brasil Ltda^®^ - http://www.emgsystem.com.br - [name]. [name])) consisting of a conditioner with a band pass filter with cut-off frequencies of 20 to 1000 Hz, an amplifier gain of 1,000 and a common mode rejection ratio > 120 dB. All data will be acquired and processed using a 16-bit analog to digital converter (EMG System do Brasil Ltda^®^ - http://www.emgsystem.com.br - [name]. [name])) at a sampling frequency of 2 kHz.

For the recording of the EMG signals, the participants will remain seated in a chair with feet apart and hands resting on the lower limbs. To standardize the EMG potentials of the four muscles analyzed with tooth contact, two strips of Parafilm M^®^ (American National Can TM, Chicago, IL, USA) will be folded into five parts (3 mm in thickness) and positioned on the first and second mandibular molars (bilateral) of each subject [40]. Four seconds of maximum voluntary clenching (MVC) will be recorded three times, with a three-minute interval between readings.

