After five minutes of rest, the recording of EMG activity will be performed three times successively under the following conditions: i) rest position: the subjects will be asked to relax and maintain the maxillary and mandibular teeth without contact; ii) maximal intercuspation (isometric): the subjects will be ask to clench the teeth as hard as possible and maintain the same level of contraction (tooth contact); and iii) chewing (isotonic): the subjects will be instructed to mildly and symmetrically bite down (chew) on the two strips of Parafilm M^®^ (positioned bilaterally) in time with a metronome adjusted to 60 beats per minute.

For the EMG signals recorded in rest position and during chewing, a two-minute interval will be allowed between readings. For maximal intercuspation, a five-minute interval between readings will be used. The data collection time will be 15 seconds for the rest position and chewing condition and 8 seconds for maximal intercuspation.

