### Pilot studies

The sample size and stabilometric variables to be used in the study were defined in two independent pilot studies, as described below:

a) Sample description and characterization: pilot study 1. The sample was defined based on a pilot study involving eight women (mean age: 23.16 ± 3.61 years) with TMD, as diagnosed using the RDC/TMD (described in the Procedures subsection). The good reliability and reproducibility of EMG signal in the evaluation of the muscles of mastication [42-45] was the main criterion for the choice measure to calculate the sample size in the proposed study.Thus, the sample size was calculated considering the largest standard deviation (SD) and root mean square (RMS) of the normalized amplitudes of the EMG signal of the right and left masseter and temporal muscles. The data were collected during maximum intercuspation for eight seconds before (T0) and after five sessions of nonspecific mobilization (T1). Considering a statistical power of 0.80, the right temporal muscle determined the largest sample (13 individuals (T0 = 1.19; T1 = 1.08; SD = 0.14)). The sample will be made up of male and female individuals, between 18 and 36 years of age, selected based on the eligibility criteria and diagnosed with TMD based on the RDC/TMD.

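### Dividing chewing EMG by the peak of the same chewing trial cancels any proportional change in amplitude, so that outcome shows the pattern of activity but not its level

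*Protocol article*

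**What the plan says.** EMG is recorded from four muscles (right and left masseter and anterior temporal) in three conditions: rest, maximal intercuspation and chewing.

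- **Chewing** (Surface electromyographic data): "The data recorded during chewing will be normalized by the peak EMG recorded from the same isotonic trial (dynamic mean method". Participants bite mildly on Parafilm strips "in time with a metronome adjusted to 60 beats per minute".
- **Rest and maximal intercuspation** (same section): amplitude is "expressed as percentage of the average RMS recorded in the three readings during maximum voluntary contraction (MVC) (%MVC".
- **The reference recordings** (Surface EMG) are made on Parafilm in the same four muscles: "Four seconds of maximum voluntary clenching (MVC) will be recorded three times, with a three-minute interval between readings".
- **Purpose** (Background), as the stated aim: "determine the effect of facial massage and mandibular mobilization on EMG activity of the muscles of mastication and static balance in individuals with TMD". The proposed mechanism is "relaxation of the muscles of mastication (as assessed through surface EMG", and earlier massage studies in these patients are cited as showing "a decrease in EMG activity in the muscles".

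The article gives no other scaling for the chewing data.

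**The concern.** The rationale concerns level: the muscles relax and EMG activity falls. Chewing is the only dynamic condition in which this is examined. If each chewing trial is divided by its own peak, a fall that affects the whole trial equally lowers both parts of the ratio and leaves no trace. A larger sample does not help, because the information has been removed before the analysis.

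What is at stake is how a null chewing result is read. The Abstract and Discussion intend to classify any effect as local to the masticatory muscles, global, or generalised. The chewing outcome as processed could not contribute evidence that muscle activity level stayed the same.

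The description is also internally inconsistent. It divides by a peak but names a dynamic mean method, and the two divisors give different numbers.

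**Working it through.** **1. The plan's own figure.** Pilot studies reports that "the right temporal muscle determined the largest sample (13 individuals (T0 = 1.19; T1 = 1.08; SD = 0.14", with power 0.80. Alpha and sidedness are not stated; two-sided 0.05 is assumed here. With a within-group normal formula:

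n = (SD × (z₀.₉₇₅ + z₀.₈₀) / difference)² = (0.14 × (1.960 + 0.842) / (1.19 − 1.08))² = (0.14 × 2.802 / 0.11)² = 12.71, rounded up to 13.

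The 13 is reproduced. It comes from maximal intercuspation, so the chewing rule does not enter it. The pilot's relative change, 0.11 / 1.19 = 9.2%, serves below as one example of an effect size.

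**2. The algebra.** Let x be the chewing signal and let treatment change it to k·x. Any amplitude summary A that scales with the signal (RMS, mean rectified value, integrated EMG) gives

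A(k·x) / peak(k·x) = k·A(x) / (k·peak(x)) = A(x) / peak(x), for every k > 0.

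This matters because the article does not name the chewing summary. The five-second RMS is described for the eight-second reading, and the 200 ms window is tied to rest and intercuspation, whereas chewing lasts 15 seconds. The cancellation does not depend on which of these summaries is meant. A same-trial mean in the divisor also scales by k, so reading the label literally would not restore level.

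**3. What survives.** Check on one simulated signal of 15 s at 2 kHz with one burst per second (the article's duration, sampling rate and pacing). Burst shape (Gaussian, SD 0.12 s) and inter-burst level (0.05 of burst height) are assumptions. The first row gives values; the others give change from it.

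| Change in the signal | Raw RMS | RMS ÷ peak | Mean ÷ peak of 200 ms envelope |
|---|---|---|---|
| None | 0.4946 | 0.1224 | 0.3721 |
| Whole signal × 0.908 | −9.2% | 0.0% | 0.0% |
| Whole signal × 0.7 | −30.0% | 0.0% | 0.0% |
| Whole signal × 0.5 | −50.0% | 0.0% | 0.0% |
| Bursts only × 0.7 | −27.8% | +1.0% | +3.0% |
| Bursts 20% narrower | −10.5% | −10.0% | −10.7% |
| Inter-burst level halved | −3.5% | −1.1% | −3.5% |

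Uniform change vanishes. A fall in the bursts alone almost vanishes and moves slightly in the opposite direction. Changes of shape remain visible, wholly or in part.

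**4. An MVC reference.** If treatment multiplies chewing by k and the MVC by m, %MVC changes by the factor k / m.

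- m = 1, k = 0.7: 0.7, the full −30%.
- m = 0.908 (illustrative), k = 0.7: 0.7 / 0.908 = 0.771, so −22.9%.
- m = k: 1, no visible change.

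An MVC reference therefore recovers level to the extent that the MVC is stable, which is why the MVC itself has to be reported.

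**The case against.** The strongest reply is that a pattern measure may be a sensible choice for this task. Participants bite mildly to a metronome, so pace is controlled and force is not, and chewing level partly reflects voluntary effort. The Background places hyperactivity in these patients at rest, and rest is recorded separately and scaled to MVC. Poor relaxation between chews would show as inter-burst activity relative to the peak, which the ratio partly retains. All of this stands, and it is why the ratio is worth keeping as a pattern index. But the article does not declare chewing a pattern outcome, and it states its aim as EMG activity.

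A second reply is that an MVC reference has the same weakness if treatment changes the MVC equally. That is correct (step 4). It limits the remedy without rescuing the planned measure, which loses every proportional change whatever happens to the MVC.

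A reader might infer more than the document supports:

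- *That the rule removes every change in muscle activity, so power equals the false-positive rate.* This is true only for a proportional change. Narrower bursts or lower inter-burst activity survive, and the article does not say that treatment acts as a single factor.
- *That the EMG assessment as a whole fails.* Rest and maximal intercuspation use a reference from outside the recording.
- *That it is an error for the three conditions to be on different scales.* Data analysis names no comparison between conditions, so no stated analysis needs a common scale.

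**Conclusion.** The point holds in a limited form. As written, the chewing outcome cannot register a proportional change in amplitude of any size: the expected change is 0.0% for falls of 9.2%, 30% or 50% alike. It describes only the shape of the activity, so a null result would say nothing about activity level, which is what the Background sets out to study.

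The cancellation is algebraic and rests only on the summary scaling with the signal. The figures for shape changes rest on an assumed burst form and a single simulated signal, and show direction and rough size only. One of the three EMG conditions is affected. Rest, maximal intercuspation and the 13 are not. This is an inexpensive improvement to one outcome and does not threaten the trial.

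**What to change.** 1. Express chewing amplitude as a percentage of the mean RMS of the three Parafilm MVC recordings, as for rest and maximal intercuspation, and name the chewing amplitude summary and its time window.
2. State which evaluation's MVC is the reference, and report MVC amplitude itself by group and evaluation, because a treatment effect on MVC would mask part of the change in chewing.
3. Keep the same-trial peak ratio, if wanted, as a secondary index described as measuring pattern only.
4. Reconcile the label with the divisor: call it peak normalisation, or state that the divisor is the mean. Neither choice restores level, so this does not replace item 1.

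**Cost.** The signal-processing routine changes and a few lines of text are added. No new recordings are needed, since the MVC trials are already part of the procedure and are made on the material that participants chew. The price is that MVC variation between evaluations enters the chewing outcome, as it already does for the other two conditions.

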#### ***Data analysis***

The Shapiro-Wilk test will be used to test the data with regard to Gaussian distribution. Data that demonstrate parametric distribution will be expressed as mean and standard deviation (SD) values. Data with nonparametric distribution will be expressed as median and inter-quartile interval. Either repeated-measure ANOVA or Friedman’s test will be used for the intra-group analysis and either one-way ANOVA or the Kruskal-Wallis test will be used for the inter-group analysis of data with parametric and non-parametric distribution, respectively.

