## Methods/Design

### Overview of research design

A randomized, controlled, blind, clinical trial is proposed to study the effects of specific and nonspecific mandibular mobilization. The participants will be allocated to three groups through a randomization process using opaque envelopes. Each group will receive a specific form of treatment for TMD. The control group (CG) will receive massage therapy and those submitted to joint mobilization will be divided into two groups: the specific mobilization group (SMG) and the nonspecific mobilization group (NMG). Evaluations will be carried out before and after treatment using the Research Diagnostic Criteria for Temporomandibular Disorders (RDC/TMD), EMG of the masseter and temporal muscles and stabilometry.

After screening, individuals with TMD (based on the RDC/TMD) will be selected. The study will be divided into three types of treatment, three evaluations and two phases, to which all individuals will be submitted:

Evaluation 1: randomization of treatment with allocation to treatment groups, stabilometric analysis and EMG analysis, with the administration of the protocol for the respective treatment.

Evaluation 2: second stabilometric and EMG evaluation immediately following respective treatment.

Treatment phase: treatment following respective protocol.

Evaluation 3: third stabilometric and EMG evaluation and second administration of the RDC/TMD questionnaire.

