#### ***Massage and mobilization interventions***

The participants will be divided into three groups, each of which will be submitted to a different protocol. Ten sessions will be given for each treatment.

Protocol 1: massage therapy, described in Table 2; the procedure will last for 20 minutes and consist of synchronized sliding and kneading with medium pressure on the anterior temporal and masseter muscles bilaterally.

Protocol 2: nonspecific mandibular mobilization with the participant in dorsal decubitus on a cot, performed by a previously trained, experienced therapist wearing disposable gloves, who will position the fifth finger on the last molar, performing nonspecific mandibular mobilization, grade I [41], intermittently for one minute, with five repetitions. In the interval between repetitions, the participant will perform mouth opening 15 times with the tongue on the incisive papilla.

Protocol 3: specific mandibular mobilization with the participant in dorsal decubitus on a cot, performed by a previously trained, experienced therapist wearing disposable gloves, who will position the fifth finger on the last molar of the side being treated and ask the participant to lightly bite down on the finger, at which point the therapist will perform specific mandibular mobilization for the disk with reduction or without reduction:

For disk with reduction, pressure to be applied will be in the caudal direction and the oscillation will be cranial to caudal, grade I [41], intermittently for one minute, with five repetitions. In the interval between repetitions, the participant will perform mouth opening 15 times with the tongue on the incisive papilla;

For disk without reduction, pressure to be applied will also be in the caudal direction and the oscillation will be caudal to cranial, grade I [41], intermittently for one minute, with five repetitions. In the interval between repetitions, the participant will perform mouth opening 15 times with the tongue on the incisive papilla.

**Table 2 T2:** Twenty-minute facial massage protocol performed bilaterally

	
Surface sliding	3 minutes
Circular movements in counter-clockwise direction	
Anterior bundle of temporal muscle	
Kneading	3 minutes
Kneading in cranial-caudal direction	
Upper fibers of masseter muscle	
Return of hands to initial position with continuous caudal-cranial sliding of suprahyoid musculature	
Surface sliding	1 minute
Circular movements in counter-clockwise direction	

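### The within-arm tests named for three evaluations use only complete rows by default, so a missing Evaluation 3 also removes a participant from the test of the immediate change

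*Protocol article*

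**What the plan says.** The Overview of research design in the protocol article states that "The study will be divided into three types of treatment, three evaluations and two phases, to which all individuals will be submitted". Evaluation 1 holds the baseline measurements and the first application of the allocated treatment. Next comes "Evaluation 2: second stabilometric and EMG evaluation immediately following respective treatment". The treatment phase follows, and after it "Evaluation 3: third stabilometric and EMG evaluation and second administration of the RDC/TMD questionnaire". The section on the interventions adds "Ten sessions will be given for each treatment".

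For the analysis within arms, the Data analysis section says "Either repeated-measure ANOVA or Friedman’s test will be used for the intra-group analysis", the choice depending on the Shapiro-Wilk result. Between arms it names one-way ANOVA or the Kruskal-Wallis test. It names no paired two-occasion test for Evaluation 1 to Evaluation 2.

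The RDC/TMD questionnaire is given only twice, so the point concerns the EMG and stabilometric outcomes, which are measured at all three evaluations.

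**The concern.** Evaluations 1 and 2 surround a single treatment application, whereas Evaluation 3 follows a phase of repeated sessions. Any loss of participants is therefore likely to show as a missing Evaluation 3 beside valid Evaluation 1 and 2 data. Classical repeated-measures ANOVA and Friedman's test cannot use such a row. The immediate change would be tested within arms only in people who later supplied Evaluation 3, a group selected by an event after randomisation. The between-arm test at Evaluation 2 needs only that evaluation and can include everyone measured. The two stated analyses could then describe different people at the same time point.

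At stake is precision in a study whose only sample-size figure is 13. If loss is related to the response to the first session, the within-arm immediate change is also at risk of bias.

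**Working it through.** **Inputs.** From Pilot studies: "Considering a statistical power of 0.80", and "13 individuals (T0 = 1.19; T1 = 1.08; SD = 0.14" for the right temporal muscle. Assumed, because not stated: two-sided alpha of 0.05; 0.14 taken as the SD of the change; loss of 10%, 20% or 30% before Evaluation 3.

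**1. The plan's own figure.** Change = 1.19 - 1.08 = 0.11. The paired normal approximation gives n = (SD × (1.960 + 0.842) / change)² = (0.14 × 2.802 / 0.11)² = 12.71, rounded up to 13. The stated figure is reproduced as a before-after calculation on complete pairs. The article states no allowance for loss beside it.

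**2. Do the named tests need complete rows?** Data were simulated for 13 participants at three occasions, with the third value missing in 3.
- A classical repeated-measures ANOVA routine rejected the data as unbalanced.
- Friedman's test returned no result.
- Both ran once the 3 participants were removed entirely. The ANOVA then had (3 - 1) = 2 and (3 - 1) × (10 - 1) = 18 degrees of freedom, against 2 and 24 with all 13.

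Unless values are imputed, the three-occasion tests therefore discard those participants' Evaluation 1 and 2 data. A comparison of Evaluation 1 with 2 on available pairs would have kept all 13.

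**3. Precision if loss is unrelated to outcome.** The standard error grows by 1/√(1 - p) - 1:
- p = 0.10: 1/√0.90 - 1 = 5.4%
- p = 0.20: 1/√0.80 - 1 = 11.8%
- p = 0.30: 1/√0.70 - 1 = 19.5%

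As an illustration, take 13 as the rows in one within-arm comparison and round the remaining rows down. Exact paired-t power for a change of 0.11 with SD 0.14 is:

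| Assumed loss | Complete rows | Power |
|---|---|---|
| 0% | 13 | 0.74 |
| 10% | 11 | 0.65 |
| 20% | 10 | 0.60 |
| 30% | 9 | 0.54 |

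The 0.74 at 13 rows is below 0.80 because step 1 uses the normal approximation.

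**4. Direction and size if loss depends on the immediate response.** In a simulation with true change -0.110 and SD 0.14, unrelated loss left the mean in complete rows at -0.110. When the odds of loss rose e-fold per SD of poorer immediate change (assumed), the complete-row mean was -0.123, -0.134 and -0.145 at 10%, 20% and 30% loss. The shifts are 0.013, 0.024 and 0.035.

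If better responders were the ones lost, symmetry gives shifts of the same size in the other direction. Under this mechanism the shift does not depend on the true mean, so any percentage depends on the effect chosen. Against -0.110, shifts of 0.013 to 0.035 are about 12% to 32%; against an assumed immediate change of -0.055 they are about twice that. The document gives no immediate effect: the pilot's 0.11 is a change after five sessions.

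**The case against.** The strongest reply is that the Data analysis section names test families in one sentence and states no deletion rule. It does not say that all three evaluations enter one test, that incomplete participants are excluded, or that nothing is imputed. A separate paired comparison on everyone with both values is compatible with the text. Such details are commonly left to an analysis plan, and none is shown.

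This stands in part. A reader might infer that the protocol orders the removal of anyone without Evaluation 3; it does not. Nor is silence about missing data the finding. What remains is that the named methods are complete-case by default, and that the three-occasion reading is the natural one. Friedman's test is normally chosen for three or more related occasions, and no paired test is named.

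A reader might also infer that someone who stops sessions early cannot reach Evaluation 3. The document does not say so. It places Evaluation 3 after the treatment phase without making attendance depend on finishing ten sessions, and it submits all individuals to three evaluations. Inviting everyone to Evaluation 3 would largely restate the plan.

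Nor does the point show that the randomised comparison at Evaluation 2 is compromised. The within-arm tests are not randomised comparisons, and the between-arm test at Evaluation 2 is untouched. Values missing at Evaluation 3 itself are a difficulty for any method.

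**Conclusion.** The point holds as a weakness in the choice of within-arm method. If all three evaluations enter one test and nothing is imputed, valid same-day data from anyone lacking Evaluation 3 are discarded from the test of the immediate change.

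The size is conditional on loss, for which the article gives no rate:
- No loss: no effect.
- Loss unrelated to outcome: no bias, and a standard error about 5-20% larger at an assumed 10-30% loss.
- Loss related to the immediate response: bias as well, with direction and amount that the document cannot fix.

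A reader might take the simulated shifts, or a percentage from them, as the expected bias. They rest wholly on an assumed loss rate, an assumed dropout mechanism and an assumed effect, so they show only that the bias need not be negligible. That the arms differ (external massage against mobilization with a finger on the last molar) makes unequal stopping possible, but nothing in the document shows that it occurs.

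**What to change.** Replace the complete-case within-arm tests with a likelihood-based linear mixed model over Evaluations 1, 2 and 3. Use every available evaluation from all randomised participants in their allocated arm, with small-sample degrees of freedom (for example Kenward-Roger or Satterthwaite). With complete data and a compound-symmetric covariance this matches the repeated-measures ANOVA already named; with incomplete data it keeps what was measured.

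For clearly non-normal outcomes, transform the outcome, or test the Evaluation 1-to-2 change with a paired rank test on everyone with both values, so that the non-parametric route is kept. Report the complete-row repeated-measures ANOVA or Friedman's test as a sensitivity analysis.

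The cost is a change of wording and slightly more analysis work, with no extra participants or procedures. The model relies on data being missing at random. It handles loss that depends on the observed Evaluation 2 value, but not loss that depends on the unseen Evaluation 3 value.
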